**Fig. 1 Fig1:**
[figure not shown]
Schedule of enrolment, interventions, and assessments for the IMPETUS-D study. t_1_: 2-month training period**.** t_2_: 6-months follow up. t_3_: 12-months follow up

### Control group

Staff from RACFs in the control group will not receive the IMPETUS-D training but will be able to receive usual training opportunities which includes training that may be provided by the facility or health care professionals visiting the facility, or may involve no training during the trial timeframe.

### Outcome measures

#### Primary outcome

The primary composite outcome measure is: 20% reduction in proportion of hospital transfers or deaths in hospital over 6 months in the intervention group (IMPETUS-D) compared to the control group.

#### Secondary outcomes

Secondary outcomes are:
Proportion of hospital transfers or deaths in hospital over 12 monthsProportion of hospital transfers over 6 and 12 monthsProportion of deaths in RACF over 6 and 12 monthsUptake of Goals of Care plans over 6 and 12 monthsChange in knowledge and attitudes about palliative care for people with advanced dementia following training and at 6 months follow up

### Process evaluation

Discrepancies between the implementation plan and its operationalizationIntervention activities that took place and who conducted the intervention activitiesUptake of the training program: proportion of PCAs and nursing staff at the intervention sites who completed the training - number of logins, time spent on each module, number of modules completed

### Qualitative research measures

Improved staff and family perception of and satisfaction with careAcceptability of the interventionBarriers to uptake of the IMPETUS-D training programEnablers to uptake of the IMPETUS-D training program

### Data collection

Table 2 summarises the data collection methods that will be undertaken to collect primary and secondary outcome measures and baseline resident demographic and clinical data.

**Table 2 Tab2:** Outcome measures, data collection methods and time points by participant group

Participants	Time points	Methods	Variables/measures
Residents	Baseline	Review of residents’ files	Demographic and clinical data of residents, including: Age, sex, time living in RACF, chronic comorbidities, dementia diagnosis and type of dementia; current level of care and function, ACP or GOC plan in place, hospitalisations/infections/falls in previous 3 months
	6 and 12-months follow-up	Review of residents’ files	Hospital transfers and primary reason for transfer; Death and place of death; GOC plan in place; GOC plan adhered to
RACF staff	Baseline, after training period and 6-months follow-up	Validated survey qPAD	Knowledge and attitudes about palliative and EOL care for people with dementia

*Abbreviations*: *ACP* advance care plans, *EOL* end-of-life, *GOC* goals of care, *qPAD* questionnaire palliative care for advanced dementia, *RACF* residential aged care facility

Resident demographic characteristics and clinical information, including whether an advance care plan (ACP) or GOC plan is in place, will be collected from the RACF resident files. During the follow-up period, any changes in uptake of ACP or GOC plans and whether they were adhered to in relation to transfers to hospital and place of death will be extracted from RACF files.

RACF staff’s knowledge and attitudes about palliative and EOL care for people with dementia will be assessed at baseline, immediately after the training period and at 6-months follow-up using the Questionnaire on Palliative Care for Advanced Dementia (qPAD) [19]. The qPAD is a validated 2-part instrument consisting of 23-item knowledge test and 12-item attitude scale.

#### Primary outcome data

Unplanned transfers to hospital, including the primary reason for transfer, and deaths of residents, date of death and place of death (RACF, hospital, other) will be extracted from the RACF files throughout the 6- and 12-month follow up period.

### Participants and recruitment

Routinely collected data from the files of residents living permanently in the RACFs will be used in the study. Residents will not be required to undertake any additional assessments or tests and they will not be receiving any additional treatment or intervention. Residents and their family will be provided with plain language information about the study via the RACF noticeboards and newsletters.

The Project Coordinators will visit the RACFs to explain the study to staff and encourage participation. All staff will be invited to participate via email, face-to-face at staff meetings, and via notices in staff rooms. Plain language statements will be provided in hard copy and or electronically via email to all potential participants and consent obtained from those willing to participate. Participation by RACF staff is voluntary.

### Process evaluation

A mixed methods process evaluation will be conducted alongside the cluster RCT. As described in the Medical Research Council’s evaluation framework, the process evaluation will aim to ‘explain discrepancies between expected and observed outcomes, to understand how context influences outcomes, and to provide insights to aid implementation’ [17].

The aims of the process evaluation are:
(i)to explore the impact of contextual factors on the delivery and effectiveness of IMPETUS-D, including barriers and facilitators;(ii)to assess how the intervention was delivered and achieved, capturing implementation fidelity and dose; and(iii)to explore participants’ experience and responses to the intervention, including reach, acceptability, satisfaction and knowledge acquisition.

Table 3 summarises the process evaluation data collection activities by CFIR domain [16]. Qualitative and quantitative data collection methods include purposive sampling for semi-structured individual and group interviews as well as participant surveys during the pre- and post-intervention phase.

**Table 3 Tab3:** Process evaluation research questions and data collection methods by Consolidated Framework for Implementation Research (CFIR) domain

Research question	CFIR domain	Data sources and timeline
What contextual factors (barriers and facilitators) influence the delivery and impact of the intervention?	Outer setting • External policy and incentives	Pre-intervention/baseline Website search and discussions with Project Advisory Group experts to identify palliative care external policy and incentives, accreditation and standards.
	Inner setting • Structural characteristics • Learning climate • Networks and communications • Readiness for implementation	Pre-intervention/baseline Survey general managers to collect data on structural characteristics, learning climate and readiness for implementation. Project Coordinators to collect information on additional structural characteristics. Group/individual interviews with senior staff to explore current practice, networks and communications, and learning climate. During early stages of training period Project Coordinators to collect information on barriers and facilitators to implementing intervention at each intervention care home.
	Characteristics of individuals • Knowledge and beliefs	Pre-intervention/baseline Survey (qPAD) care staff to assess knowledge and beliefs on advanced dementia palliative care; barriers and enablers to providing quality advanced dementia care.
To what degree is the intervention implemented as planned? Assess recruitment, reach, dose (quantity), fidelity (quality).	Process • Planning • Engaging • Executing	During 2-month training period Participation and module completion rates via the LMS. Survey embedded in modules to assess participant satisfaction and module feedback. Project coordinator documentation of implementation activities undertaken, local challenges and strategies used to overcome issues. Shortly after the training period Semi-structured interviews with Project coordinators to explore their experience of implementation. Semi-structured group/individual interviews with staff from the intervention group to assess their experience of implementation.
How does the delivered intervention produce change? Assess participants’ responses to and interactions with the intervention, mediators and unexpected pathways and consequences.	Characteristics of individuals • Knowledge and beliefs • Individual stage of change	6-months follow up Semi-structured group/individual interviews with staff from the intervention group about their experience with and impact of the intervention. Repeat survey (qPAD) of care staff to assess knowledge and beliefs on advanced dementia palliative care.

*Abbreviations*: *LMS* learning management system, *qPAD* questionnaire of palliative care in advanced dementia

### Data management

A dedicated study database has been developed using the Research Electronic Data Capture (REDCap) electronic data capture tools hosted at the University of Melbourne [20]. REDCap is a secure, web-based application designed to support data capture for research studies, providing 1) an intuitive interface for validated data entry; 2) audit trails for tracking data manipulation and export procedures; 3) automated export procedures for seamless data downloads to common statistical packages; and 4) procedures for importing data from external sources. Paper documentation will be securely stored in a locked filing cabinet. All records will be kept for a minimum of 5 years post study completion. Only listed research staff working on the project will have access to these files.

### Power calculation

In this study 24 facilities (12 intervention sites and 12 control sites) will be recruited. The power analyses were based on the following assumptions: proportion of composite events of 0.65 and 0.85 over 6 months of follow-up in the intervention and control groups respectively, two-sided significance level of 0.05 (alpha), 12 clusters (facilities) in each study arm, 20–25 residents with dementia in each cluster, an Intra-Cluster Correlation (ICC) of 0.05. With these assumptions, the minimum power to observe a difference of proportion by 0.20 between the intervention and control group is 94%. If the number of residents with dementia per cluster reduces to 15 only, the power to observe this difference reduces to 0.93%. If the cluster size in each group is reduced to 10 and the number of residents in each cluster is only 15, then the study would have a power of 88% to observe a difference in proportion by 0.20.

The assumptions on the composite of events for this study were based on the information reported in the study by RS Martin (2017) [21].

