## Discussion

With the ageing population, the number of people with dementia is expected to increase, and so too will the need for high quality advanced dementia care delivered in RACF settings. This cluster RCT will evaluate the effectiveness of an innovative screen-based simulation training program on caring for people with advanced dementia, aimed at staff working in the residential care setting. This large multisite trial will provide robust evidence about the impact of the intervention.

In this study we assess a new and innovative screen-based simulation training program. The training program is designed to address the current status of the RACF workforce in Australia, including high staff turnover, varying skill sets and literacy levels. The training resource has been developed with input from the end-users and subject matter, education and simulation experts. Furthermore, being screen-based and accessible online will allow the often time poor residential care workers, greater convenience and opportunity to participate.

The modules include narratives derived from experts’ experiences and in consultation with residential care staff. The modules aim to achieve functional task alignment (the simulator does what is required to meet the learning objective) and learner engagement (the extent to which the learner participates or ‘buys-in’ to in the activity to meet the learning objective) – two concepts considered more valuable than ‘fidelity’ [22]. The narratives went someway to addressing these concepts through development with those intimately acquainted with this work from provider and user perspectives, by shooting the videos and selected still images in local facilities and seeing and hearing the voices of actual care staff in narratives.

The generalisability of findings from studies involving multiple RACFs is always a challenge. However, various aspects of heterogeneity of the RACFs in different Australian cities have been considered in this cluster randomised study, and block design in the randomisation has been used. The study is adequately powered under different possibilities, allowing us to draw robust inference.

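### The three printed power figures (94%, 0.93%, 88%) contain a misprint and, even with it corrected, do not come from one calculation on the stated inputs

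*Protocol article*

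**What the plan says.** The Power calculation section assumes "proportion of composite events of 0.65 and 0.85 over 6 months of follow-up in the intervention and control groups respectively", a two-sided 5% level, "12 clusters (facilities) in each study arm", "20–25 residents with dementia in each cluster" and an ICC of 0.05. It then reports three results:

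- Base case: "the minimum power to observe a difference of proportion by 0.20 between the intervention and control group is 94" per cent.
- Fewer residents: "If the number of residents with dementia per cluster reduces to 15 only, the power to observe this difference reduces to 0.93", printed with a per cent sign.
- Fewer homes as well: "If the cluster size in each group is reduced to 10 and the number of residents in each cluster is only 15", for which the power is given as 88%.

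No formula or software is named. The Statistical methods section plans logistic regression with standard errors that allow for clustering. The Discussion draws on the scenarios: "The study is adequately powered under different possibilities, allowing us to draw robust inference".

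**The concern.** Two slips are visible without any calculation. A power of 0.93% is impossible between 94% and 88%. The last scenario also applies the term cluster size to the value 10 and then gives 15 residents per cluster, so read literally it states two different cluster sizes.

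The less visible problem is the size of the steps. Reading the misprint as 93%, the loss of a quarter of the residents in every home appears to cost one percentage point. With an ICC of 0.05 and only 12 homes per arm, that is too small a loss. The fallback scenarios are there to show how much shortfall the trial can tolerate, and the Discussion relies on them. If the three figures come from different approximations, a reader cannot tell how much power a shortfall would really cost.

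**Working it through.** **Inputs** (all from the Power calculation section): proportions 0.65 and 0.85; two-sided alpha 0.05; ICC 0.05; scenarios of k homes per arm with m residents each, namely 12×20, 12×15 and 10×15. In the base case the lower end of the 20–25 range gives the minimum power.

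**Effective sample size per arm**, n = k·m / [1 + (m − 1)·0.05]:

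- 12×20: 240/1.95 = 123.1
- 12×15: 180/1.70 = 105.9
- 10×15: 150/1.70 = 88.2

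**Reproducing the printed figures.** For an unpooled z test the variance term is 0.65·0.35 + 0.85·0.15 = 0.355, and z = 0.20/√(0.355/n):

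- z = 3.72, 3.45 and 3.15
- power = Φ(z − 1.96) = 96.1%, 93.2% and 88.4%

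This reproduces 93 and 88, but not 94. Referring the same statistic to a noncentral t with 2(k − 1) = 22, 22 and 18 df gives 94.5%, 91.0% and 84.6%. This reproduces 94, but not 93 or 88.

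**Other methods on the same inputs** (power, %):

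| Method | 12×20 | 12×15 | 10×15 | Loss, 20 to 15 residents |
|---|---|---|---|---|
| Printed (0.93% read as 93%) | 94 | 93 | 88 | 1 |
| Unpooled z | 96.1 | 93.2 | 88.4 | 2.9 |
| z, pooled variance under the null | 95.6 | 92.5 | 87.3 | 3.1 |
| Arcsine | 95.8 | 92.9 | 87.8 | 2.9 |
| Noncentral t on the difference | 94.5 | 91.0 | 84.6 | 3.5 |
| Log-odds Wald z | 94.3 | 90.7 | 85.0 | 3.6 |
| Log-odds Wald, noncentral t | 92.2 | 88.0 | 80.9 | 4.2 |
| Simulated logistic, cluster-robust SE, z reference | 95.3 | 92.5 | 87.3 | 2.8 |
| Simulated logistic, cluster-robust SE, t on 22 or 18 df | 94.1 | 90.7 | 84.0 | 3.4 |

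The simulations used beta-binomial data with ICC 0.05 and 40,000 trials per scenario.

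**Consistency check that hardly depends on the method.** Going from 20 to 15 residents multiplies z by √(105.9/123.1) = 0.928. On the normal scale:

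- 94% at 20 residents means z = 1.555 + 1.960 = 3.515. At 15 residents z = 3.515 × 0.928 = 3.26, so power is about 90%. For 10×15, z = 3.515 × √(88.2/123.1) = 2.98, so power is about 85%.
- 93% at 15 residents means z = 1.476 + 1.960 = 3.436. At 20 residents z = 3.436/0.928 = 3.70, so power is about 96%.

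Rounding does not explain the gap. A printed 93 can stand for 92.5 to 93.5, which implies 95.6 to 96.3 at 20 residents. A different ICC does not explain it either. Over ICC values from 0 to 0.15, the best fit of any formula tried still missed at least one printed figure by about 1.2 points (unpooled z at ICC 0.056: 95.2/92.1/86.8).

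**Which figure is the odd one out.** The printed step from 12×15 to 10×15 is 5 points. The unpooled z test gives 93.2 − 88.4 = 4.8 and arcsine gives 92.9 − 87.8 = 5.1. So 93 and 88 are consistent with each other under these methods, and the 94 does not belong with them.

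**The case against.** The strongest reply is that nothing material is wrong. The 0.93% is an obvious unit slip and cluster size an obvious slip of terminology. The pooled-null z test and the arcsine test each come within 2 points of all three printed figures, and the article names no method against which whole-percent agreement could be demanded. The 94% is called a minimum, so a true value near 96% would not contradict it.

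Much of this stands. The figures are close to what ordinary methods give, and a conservative headline beside two correct fallbacks is a fully plausible reading. But a tolerance of 2 points cannot test a printed step of 1 point, and every method tried puts that step at about 3 to 4 points. At least one printed figure is therefore off for the stated inputs.

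A reader might infer two stronger things. The first is that the fallback scenarios are definitely overstated. That requires taking 94% as the correct anchor, or assuming a t reference. The article says neither, and two of its three figures fit the z or arcsine reading. The second is that the planned logistic analysis would have some 6 points less power than printed in the worst scenario. A gap of that size needs a small-sample correction beyond a t reference with the usual cluster-robust variance, or the log-odds Wald approximation with noncentral t (80.9% against 88%). The Statistical methods section specifies neither, and that choice commonly belongs to an analysis plan that is not shown. In the simulations above, the largest shortfall is 88 − 84.0 = 4 points with the t reference and under 1 point with the z reference.

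**Conclusion.** The point holds in a limited form. One power figure is misprinted, one term is wrong, and the three figures do not belong to a single calculation on the stated inputs. Either 94% is about 2 points low, with 93% and 88% right under a z or arcsine test, or 94% is right and the fallbacks are about 2 and 3 to 4 points high under a t-referenced or log-odds calculation. The document does not decide between these. What does not depend on that choice is the cost of falling from 20 to 15 residents per home: about 3 to 4 points, against the printed 1.

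This rests on the stated proportions and ICC, on equal cluster sizes and on the usual design effect. The lowest variant tried gives 80.9% in the worst scenario, so the sample size stands, and so does the Discussion's claim of adequate power once it rests on restated figures.

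**What to change.** In the Power calculation section:

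1. Correct 0.93% to a proper percentage.
2. In the last scenario, write that the number of clusters in each group is reduced to 10.
3. Recompute all three scenarios by one method and name it.

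The preferable method matches the logistic analysis in the Statistical methods section, with a reference distribution that reflects the 20 to 24 homes. In the simulations a z reference had a null rejection rate of about 7%, against about 5% with t. On that basis the figures would be about 94%, 91% and 84–85%. If the authors used, and prefer to keep, a two-proportion z or arcsine calculation, the consistent set is about 96%, 93% and 88%, and the headline is the figure to change. The Discussion sentence should then rest on whichever set is printed.

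The cost is a few figures, one phrase and one clause naming the method. The design and the sample size do not change.

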### Statistical methods

All analyses will be conducted on an intention-to-treat basis. The basic statistics will be presented by number (%), mean (SD), median (Q1, Q3), mean (95% CI) or median (95% CI of median), as appropriate. For analyses of primary and secondary outcomes, the fundamental principle of analysing data from cluster randomised trials will be followed, where appropriate adjustments for cluster level variations will be accounted for to ensure robust inferences.

To compare the proportion of composite events for the primary outcome and the proportions for individual components of the primary outcome (secondary outcomes), logistic regression models will be used with standard errors weighted by the cluster effects. The uptake of GOC is a binary measure at the individual resident level, and will be analysed using logistic regression. Odds ratios and 95% confidence interval will be presented, along with the *p* value, for comparison between intervention and control groups. The change in RACF staff’s knowledge and attitudes about palliative and EOL dementia care immediately following the training period and at 6-months from baseline will be measured using the qPAD. The median change in qPAD score immediately following training and at 6-months follow-up will be compared between the study groups using quintile regression model (adjusted for cluster effects). All statistical tests will be two-sided with a significance level of 0.05.

Additional exploratory analyses will be conducted to evaluate the primary and secondary outcomes of the study, adjusting for potential confounders such as age, sex and comorbidities.

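### With 24 facilities, the named cluster-adjusted logistic analysis would test at about 7% rather than 5% if run in its usual form, so a small-sample correction should be specified

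*Protocol article*

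**What the plan says.** Statistical methods fixes the model for the primary composite and for its components: "logistic regression models will be used with standard errors weighted by the cluster effects". The abstract repeats this for the primary analysis. The same section sets the level: "All statistical tests will be two-sided with a significance level of 0.05". It also makes a general commitment to adjust suitably for variation between clusters. GOC uptake is to be analysed by logistic regression, and change in qPAD score by a regression of medians adjusted for cluster effects.

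Power calculation gives the number of clusters: "24 facilities (12 intervention sites and 12 control sites) will be recruited". The section assumes "20–25 residents with dementia in each cluster" and "an Intra-Cluster Correlation (ICC) of 0.05". Recruitment of RACFs sets a minimum of 20 eligible residents per facility and no maximum. Randomisation and blinding stratifies by city and by facility size.

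The article does not name the variance estimator, the reference distribution or any allowance for the small number of facilities, and it does not rule one out.

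**The concern.** The natural reading of the quoted method is an ordinary logistic model with cluster-robust (sandwich) standard errors. No random effect or facility-level analysis is mentioned. Two things go wrong with that method when clusters are few. First, the sandwich variance is biased downward, because each facility's residual is measured from an arm proportion that the same facility helped to determine. Second, the variance is estimated from only 24 facilities, so the statistic has heavier tails than the normal distribution. Both push towards rejection.

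One primary test decides the trial, and the Discussion ties national availability of the programme to a demonstration of effectiveness. A test that exceeds its stated level would overstate a borderline positive result.

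**Working it through.** **Inputs from the article:** "12 clusters (facilities) in each study arm"; 20–25 residents per facility; ICC 0.05; "proportion of composite events of 0.65 and 0.85 over 6 months of follow-up in the intervention and control groups respectively"; two-sided 0.05.

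**Assumptions not in the article:** beta-binomial facilities; null event rates from 0.3 to 0.85; coefficient of variation (CV) of facility size of 0, 0.4 or 0.7.

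**Step 1: the article's power figures.** Effective n per arm = k·m / [1 + (m − 1)·ICC]. For 12×20 this is 240/1.95 = 123.1; for 12×15, 180/1.70 = 105.9; for 10×15, 150/1.70 = 88.2. The unpooled normal formula is Φ(0.20·√n / √(0.65·0.35 + 0.85·0.15) − 1.96), where the root in the denominator is √0.355 = 0.596. The pooled version replaces 1.96 by 1.96·√(2·0.75·0.25)/0.596. The t version uses a noncentral t with 2(k − 1) df.

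| Facilities per arm × residents | Stated | Normal, pooled / unpooled | t, pooled / unpooled |
|---|---|---|---|
| 12×20 | 94% (minimum) | 95.6% / 96.1% | 93.3% / 94.5% |
| 12×15 | 93% (printed as 0.93%) | 92.5% / 93.2% | 89.4% / 91.0% |
| 10×15 | 88% | 87.3% / 88.4% | 82.7% / 84.6% |

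The stated figures are reproduced within 2 points. The two smaller scenarios match a normal reference and not a t. The 94% does not discriminate, because a continuity-corrected normal formula also gives 94.0%.

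**Step 2: hand check of the type I error.** In the unadjusted model the sandwich variance of the log odds in one arm is Σ(yᵢ − mᵢp̂)² / [Σmᵢ p̂(1 − p̂)]², and the two arms are added. With 12 equal facilities per arm, the expected squared residual is shrunk by about 11/12, so the standard error is about √(11/12) = 0.957 of its target. Comparing with 1.96 then amounts to comparing a roughly t(22) statistic with 1.96 × 0.957 = 1.877, which has a two-sided tail of 7.4%. The factor G/(G − 1) = 24/23 raises the cut-off only to 1.917, a tail of 6.8%.

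**Step 3: simulation under the null** (40,000 replicates per setting, ICC 0.05, 20–25 residents on average, unadjusted model; Monte Carlo standard error about √(0.07·0.93/40,000) = 0.13 points).

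| Variance and reference | Equal sizes | CV 0.4 | CV 0.7 |
|---|---|---|---|
| Sandwich, normal | 7.0–7.8% | 7.9–8.4% | 9.1–9.5% |
| × G/(G − 1), normal | 6.5–7.2% | 7.4–7.8% | 8.4–8.9% |
| × G/(G − 1), t(23) | 5.2–5.8% | 6.0–6.4% | 7.0–7.5% |
| Kauermann-Carroll type, t(22) | 4.7–5.2% | 5.2–5.8% | 5.8–6.3% |

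A Mancl-DeRouen-type correction with t(22) gives 4.0–4.9% across the three columns. A separate simulation with unequal facilities that all have 20 or more residents gives 7.1–8.1% for the two normal-reference forms. The result hardly depends on the ICC: with 22 residents, equal sizes and an event rate of 0.85, the uncorrected sandwich gives 7.4% at ICC 0.01 and 7.9% at 0.10.

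**Step 4: interval width.** With equal sizes the uncorrected standard error averages 0.92–0.95 of the true one, and 1.96/2.074 = 0.945. The product is 0.87–0.90, so the interval is 10–13% too narrow. With the G/(G − 1) factor the ratios are 0.94–0.97 and the shortfall is about 8–11%.

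**The case against.** The strongest objection is that the missing correction is read from silence. The wording on cluster-weighted standard errors is not a standard term for an uncorrected sandwich. The article does not state a normal reference, and nothing in it conflicts with a corrected variance or a t distribution. It is a condensed article, the analysis plan is not shown, and such detail is often left to that plan. This stands as far as it goes: a reader might infer that the trial's true type I error is 7–9%, and the documents do not show that.

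Three further inferences also lack support.

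- Rates near 9% need either strongly varying facility sizes or city and size in the model (8.7–9.9% in simulation, with and without the G/(G − 1) factor). The article gives no size distribution. The only covariates that it names are age, sex and comorbidities as examples, and those are for exploratory analyses.
- Ten facilities per arm is a sensitivity scenario for power and not a fallback design.
- Over-rejection in every secondary test does not follow, because the median regression of qPAD was not simulated.

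The match of the smaller power scenarios to a normal reference is evidence about planning only.

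The objection does not remove the point. The article names a method and a level, and the method as ordinarily run does not hold that level with 24 facilities. This is therefore more than a request to write down an omitted detail.

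**Conclusion.** The concern holds conditionally. If the named analysis is run with a cluster sandwich variance, at most a G/(G − 1) factor and a normal reference, its type I error is about 7% with equal facilities of 20–25 residents. It is about 7–8% with moderately unequal sizes, and 95% intervals are roughly 10% too narrow. The equal-size figure uses the article's number of facilities, facility size and ICC. The unequal-size figure also rests on an assumed size distribution, although a minimum of 20 residents with no maximum makes some inequality likely.

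The excess is modest and matters mainly for a borderline result. The design is not in question: the stated 94% power essentially survives a t reference. The point should be settled before the data are analysed.

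**What to change.** For the primary composite and the other binary resident-level outcomes, GOC uptake included, specify a small-sample-corrected cluster-robust variance (for example Kauermann-Carroll). Use a t reference on the number of facilities minus the number of facility-level parameters: 24 − 2 = 22 df if unadjusted. An equivalent facility-level analysis would also serve. If facility sizes turn out to vary strongly, Kauermann-Carroll can still run slightly high (5.8–6.3% at CV 0.7), and a Mancl-DeRouen-type correction is the more conservative choice. For the qPAD medians, name a cluster-level method suited to few clusters; the correction above is not designed for a median regression. If the analysis plan already contains such a rule, it is enough to confirm it.

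The cost is a sentence or two, standard software and slightly wider intervals. With a t reference, power at 12×20 is 93.3–94.5%. The smaller scenarios fall to about 89–91% (12×15) and 83–85% (10×15), against the stated 93% and 88%.

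### The qPAD comparison uses the baseline score only by subtraction and rests on a coarse median, so it is valid but less precise than the collected data allow

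*Protocol article*

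**What the plan says.** The Statistical methods section of the protocol article takes change in qPAD from baseline as the measure, at the end of training and at six months. The median change "will be compared between the study groups using quintile regression model (adjusted for cluster effects"). No other term in that model is named.

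The Data collection section says: "The qPAD is a validated 2-part instrument consisting of 23-item knowledge test and 12-item attitude scale". It gives no scoring rule. Table 2 lists the staff survey at "Baseline, after training period and 6-months follow-up", so a baseline score is collected.

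Statistical methods also plans exploratory analyses of the primary and secondary outcomes, "adjusting for potential confounders such as age, sex and comorbidities". Baseline qPAD is not among these examples.

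**The concern.** There are three difficulties.

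- **Name of the method.** 'Quintile' regression does not describe a comparison of medians. Quantile regression at the median is evidently meant.
- **Use of baseline.** A change score fixes the coefficient of the baseline score at 1. Unless baseline and follow-up are almost perfectly correlated, that is not the most efficient coefficient, and estimating it costs nothing because the score is already in hand.
- **Coarseness.** If the 23-item knowledge test is scored as the number of correct answers, change is a whole number with many ties. A difference between two medians of such data moves in steps and can stay at zero while the distributions shift.

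Staff knowledge and attitude are the outcome closest to what the training teaches, and the process evaluation (Table 3) uses the same survey to examine how the intervention produces change. An imprecise or stepwise estimate would weaken that link in the interpretation.

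**Working it through.** **What the documents supply.** They supply the contrast (median change), the adjustment (cluster only), the survey times and the item counts. For qPAD they give no SD, correlation, distribution, staff numbers, staff-level ICC, target difference or power, so there is no planned qPAD figure to reproduce. The 94% power in the Power calculation section concerns the primary outcome and does not bear on this point. Every r, SD and ICC used below for qPAD is therefore an assumption.

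**Step 1: cost of omitting the baseline covariate.** Let baseline and follow-up have equal variance σ² and correlation r.

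- Variance of change: 2σ²(1−r).
- Residual variance after adjustment for baseline: σ²(1−r²).
- Ratio: 2(1−r)/(1−r²) = 2/(1+r).

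**Step 2: cost of a median in place of a mean.** For normal data in large samples, var(median)/var(mean) = π/2 = 1.571.

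**Step 3: joint factor.** This is (π/2) × 2/(1+r). The standard error ratios are the square roots.

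| Assumed r | Baseline omitted: variance (SE) | Joint with median: variance (SE) |
|---|---|---|
| 0.3 | 1.54 (1.24) | 2.42 (1.55) |
| 0.5 | 1.33 (1.15) | 2.09 (1.45) |
| 0.7 | 1.18 (1.08) | 1.85 (1.36) |

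At r = 0.9 the joint factor falls to 1.65.

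**Step 4: simulation with clusters and ties.** The assumed setting was 12 facilities per arm with 20 staff each, mean 14 and SD 3.5. Integer scores were limited to 0–23. The comparison is the variance of the median-change difference over that of the baseline-adjusted mean difference.

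| ICC 0.05 | r = 0.3 | r = 0.5 | r = 0.7 |
|---|---|---|---|
| Continuous scores | 1.94 | 1.71 | 1.50 |
| Integer scores | 2.44 | 2.13 | 1.37 |

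With integer scores and r = 0.5, varying the true difference from 0 to 1.5 items gave ratios of 2.09 to 2.58. With integer scores, ICC 0 and r = 0.7, the ratio reversed to 0.72.

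A smaller run (300 repetitions per setting) explains the reversal. In that same setting the root mean squared errors, median against adjusted mean, were 0.22 against 0.24 at a true difference of 0, 0.16 against 0.21 at exactly 1 item, and 0.51 against 0.23 at half an item. The tied median does well when the truth is a whole item and badly when it lies between.

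**Step 5: coarseness.** With integer scores, 92–99% of simulated median differences were whole numbers and the rest were half-points. With a true difference of 0.5 items (r = 0.5, ICC 0.05, 3,000 runs), the median difference was exactly 0 in 43% of runs. The baseline-adjusted mean difference averaged 0.49.

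**The case against.** The strongest reply is that nothing here is invalid. Randomisation makes a comparison of change scores sound, and on a bounded test with skew or a ceiling a median is defensible. The list of exploratory covariates is open-ended, so baseline qPAD could still be added. The outcome is secondary and has no power claim attached. All of this stands, and it limits the point to precision and coarseness. It does not answer why a collected baseline score is left out of the named model, and the article gives no reason of skew or ceiling for the median.

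A reader might infer more than the documents support:

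- *Lack of baseline adjustment doubles the variance.* It does not. Alone it gives about 1.2 to 1.5; a doubling needs the median factor too, near-normal scores and r of about 0.5 to 0.6.
- *The estimate can move only in whole items.* Half-items also occur, further covariates can give fractional coefficients, and number-correct scoring is itself assumed. For the attitude scale the unit would be a scale point.
- *Knowledge and attitudes are merged into one score.* The text uses a singular score but nowhere says that the two parts are summed, and it calls the instrument two-part.
- *Unpaired responses are thrown away.* The Discussion describes the workforce as "including high staff turnover, varying skill sets and literacy levels", and a change score does need both surveys from one person. But the outcome is defined as change, and missing-data handling may be settled in an analysis plan that is not shown. Adding staff who joined after randomisation would bring its own selection risk.
- *The standard errors will be unreliable with ties.* The article says only that clusters are adjusted for. A cluster bootstrap would fit that wording.

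**Conclusion.** The point holds as one of efficiency and resolution in a secondary outcome. The named analysis is valid under randomisation, but it uses the baseline score less well than it could. That alone costs a variance factor of 2/(1+r), or 1.18 to 1.54 for assumed r of 0.7 to 0.3. With use of a median, and if scores are roughly normal, the joint factor is about 1.8 to 2.4. Clustering can make it smaller (1.37 to 1.50 at r = 0.7), and with tied scores it depends on where the true difference falls and can reverse. The coarseness rests on number-correct scoring, and the 43% figure holds only for the assumed simulation setting. None of these sizes comes from the documents. The misnamed method is plain on the page. The primary analysis and its power are unaffected.

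**What to change.** 1. Correct 'quintile' to 'quantile' in Statistical methods.
2. Analyse the follow-up knowledge score and the follow-up attitude score, each with its own baseline score as a covariate and adjustment for facility clustering.
3. Preferably report an adjusted mean difference at each of the two time points and keep the median comparison as a sensitivity analysis.
4. If the median stays as the main analysis because skew or a ceiling is expected, give that reason and still include the baseline score.

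The cost is wording only, as no new data are needed. The one downside is that the headline may become a mean rather than a median difference.
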